## Abstract

**Background:**

Maintaining a healthy weight and undertaking regular physical activity are important for the secondary prevention of cardiovascular disease (CVD). However, many people with CVD are overweight and insufficiently active. In addition, in Australia only 20-30% of people requiring cardiac rehabilitation (CR) for CVD actually attend. To improve outcomes of and access to CR the efficacy, effectiveness and cost-effectiveness of alternative approaches to CR need to be established.

This research will determine the efficacy of a telephone-delivered lifestyle intervention, promoting healthy weight and physical activity, in people with CVD in urban and rural settings. The control group will also act as a replication study of a previously proven physical activity intervention, to establish whether those findings can be repeated in different urban and rural locations. The cost-effectiveness and acceptability of the intervention to CR staff and participants will also be determined.

**Methods/Design:**

This study is a randomised controlled trial. People referred for CR at two urban and two rural Australian hospitals will be invited to participate. The intervention (healthy weight) group will participate in four telephone delivered behavioural coaching and goal setting sessions over eight weeks. The coaching sessions will be on weight, nutrition and physical activity and will be supported by written materials, a pedometer and two follow-up booster telephone calls. The control (physical activity) group will participate in a six week intervention previously shown to increase physical activity, consisting of two telephone delivered behavioural coaching and goal setting sessions on physical activity, supported by written materials, a pedometer and two booster phone calls. Data will be collected at baseline, eight weeks and eight months for the intervention group (baseline, six weeks and six months for the control group). The primary outcome is weight change. Secondary outcomes include physical activity, sedentary time and nutrition habits. Costs will be compared with outcomes to determine the relative cost-effectiveness of the healthy weight and physical activity interventions.

**Discussion:**

This study addresses a significant gap in public health practice by providing evidence for the efficacy and cost-effectiveness of a low cost, low contact, high reach intervention promoting healthy weight and physical activity among people with CVD in rural and urban areas in Australia. The replication arm of the study, undertaken by the control group, will demonstrate whether the findings of the previously proven physical activity intervention can be generalised to new settings. This population-based approach could potentially improve access to and outcomes of secondary prevention programs, particularly for rural or disadvantaged communities.

**Trial Registration:**

ACTRN12610000102077

## Background

Cardiovascular disease (CVD) is the leading cause of death in Australia [1] and contributes significantly to health costs [2]. Maintaining a healthy weight and participating in regular physical activity are important for the secondary prevention of CVD [3]. However many people with CVD are overweight and physically inactive [4,5]. Despite the benefits of attending cardiac rehabilitation (CR) [6,7] many people with CVD continue to be insufficiently physically active regardless of their attendance at CR [8], and there is little evidence of weight loss occurring as a result of CR attendance [9,10]. Of additional concern is that 70-80% of those requiring secondary prevention for CVD do not attend CR [11-13] leaving the majority of people with CVD with unmet health needs. People that do not attend CR are likely to need it more as they have higher risk factor profiles, poorer risk factor knowledge [14] and live further from CR services than those who attend [15].

Thus the challenge is to improve health outcomes for the majority of people with CVD who do not attend CR. In response to this challenge, investigating alternative service models for delivering CR programs shows promise [16]. To determine the characteristics of effective CR, Clark et al conducted a meta-regression of secondary prevention programs for people with CVD. They concluded that shorter programs delivered by generalist staff in non-hospital settings were at least as effective in reducing mortality as the conventional longer CR programs delivered by specialists in hospital settings [17]. Home-based CR has also been found to be as effective as centre-based CR held in settings such as hospitals, gymnasiums or community centres [18].

Distance interventions, delivered remotely via print, telephone or internet, are likely to have improved population reach, accessibility, cost-effectiveness and maintenance of gains at follow-up compared to centre-based programs [19]. Systematic reviews of distance interventions for increasing physical activity [19], telephone-based interventions for promoting physical activity and dietary change [20], and interventions using pedometers to increase physical activity [21] provide support for the effectiveness of these types of interventions, however conclusions are limited by the quality of the studies assessed. Combining delivery modes for distance interventions, such as using printed educational materials together with pedometers and telephone support, is likely to be most effective [19,20,22].

Reports of interventions promoting healthy weight and physical activity in people with CVD are scarce. A recent Australian study identified significant benefits of a telephone-delivered, pedometer-based intervention on physical activity levels among people with cardiac disease who attended outpatient CR [23]. Another Australian study reported that coaching using telephone and written materials was effective in reducing the body mass index (BMI) of cardiac patients [24]. For overweight patients attending CR, a high-volume, high energy expenditure physical activity program (60-90 minutes per session five-seven days per week) resulted in significant weight reduction compared to standard CR [25,26].

Even fewer interventions address the majority of cardiac patients who do not attend CR. The CHOICE program included a face-to-face consultation and four follow-up phone calls and was effective in improving cardiac risk factors for people with cardiac disease who had not attended CR [5]. Furber et al found that a pedometer-based telephone intervention increased physical activity levels in cardiac patients who did not attend a CR program [27].

Cost effectiveness analyses are rarely conducted on health care interventions [28] and to our knowledge no cost-effectiveness studies of Australian CR programs have been published. A meta-analysis of 63 secondary prevention programs for people with CVD found that few studies published any data on costs and conclusions about cost-effectiveness could not be made [29]. Information on cost-effectiveness of health interventions is useful before health programs are widely implemented. It is recommended that CR research evaluate economic outcomes alongside clinical outcomes [29].

## Methods/Design

### Study design

This study is a randomised controlled trial comparing the efficacy of a healthy weight telephone coaching intervention (intervention group) with a physical activity telephone coaching intervention (control group). An outline is shown in Figure 1. The control group will also act as a replication study of a telephone-based physical activity intervention previously shown to be efficacious [13,27], and will build on the evidence base by determining whether the findings of the previous study [13,27] can be generalised to diverse settings. An additional advantage of this design is that the attention-focused control group will reduce possible Hawthorne effects (where participants change their performance in response to being observed [30]) for the intervention group in this study.

**Figure 1 F1:**
[figure not shown]
**Design of the PANACHE study**.

Approval to conduct this research has been granted by the Human Research Ethics Committees from University of Wollongong, South Eastern Sydney and Illawarra Area Health Service, Greater Southern Area Health Service and the University of New South Wales. 

### Participants

All people referred to outpatient CR over a 12-18 month period at two Sydney and two NSW rural hospitals in Australia will be invited to participate in the study, whether or not they attend outpatient CR. Based on a previous Australian study [13], it is anticipated that of those invited to the study 29% will attend outpatient CR, while 71% will not attend CR. Participants will be excluded if they have any of the following: a clinical diagnosis of uncompensated, severe cardiac failure (Class IV); uncontrolled arrhythmia or angina; severe or symptomatic aortic stenosis; persistent hypotension; a clinical diagnosis of a severe coexisting medical condition that would prevent participation (eg. cognitive impairment, dementia, a terminal illness, severe rheumatoid arthritis, severe arthritis, renal disease requiring dialysis, uncontrolled diabetes); major orthopaedic surgery likely to affect mobility planned within the next 6 months (eg. hip replacement; knee reconstruction; spinal surgery); insufficient English to participate in the telephone coaching calls; non-return of a signed participant consent form and/or a signed doctor's clearance form.

Participants will be recruited six-eight weeks after referral to CR by which time they would be likely to be clinically stable in their recovery process. Brief written information about the study will be included in the information packs distributed to people referred to CR. A personalised invitation letter will also be mailed, followed up with a telephone call.

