### Randomisation and blinding

During the follow up telephone call participants will be randomised by the researcher into intervention and control groups when they agree to be enrolled in the study. Participants will be block randomized within site. Microsoft Excel will be used to generate random numbers and the Statistical Analysis System (SAS) will be used to randomise these numbers into sets of two letters (A and B, representing the intervention and control groups respectively) by blocks of four to ensure a balanced sample size across both study groups [31]. The random numbers will be generated and packaged by a person external to the study so the group allocation will be concealed from the researcher until the participant has agreed to be in the study [32]. Participants will not be told whether they have been allocated to the intervention or control group and will remain blinded to group allocation. Group allocation will not be concealed from the researcher when delivering the intervention or assessing outcomes.

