### Statistical analysis

The analyses of the trial will be based on (i) intention to treat and (ii) treatment received. Bivariate and multivariate analyses will assess the effects of the intervention (compared to controls) on weight loss, sedentary behaviour, nutrition and physical activity adjusted for residence (rural or urban), age and sex for all cases and then treatment received after initial intention to treat analysis. Continuous data will be analysed with paired t-tests and linear regression and categorical variables with chi square tests and logistic regression with p < 0.05 as the level of significance but adjusted appropriately when multiple testing is conducted. Analyses will be performed with PASW 18.0 (SPSS Inc., Chicago, IL). Food diaries will be analysed using FoodWorks 2007 (Xyris Software).

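### Allocation is opened on agreement in the recruitment call, but missing signed forms are an exclusion, so people can be excluded after allocation is known

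*Protocol article*

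**What the plan says.** All references are to the protocol article.

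- **Participants.** The list of exclusions ends with "non-return of a signed participant consent form and/or a signed doctor's clearance form". For recruitment, brief information goes into the packs given to people referred to cardiac rehabilitation, and then: "A personalised invitation letter will also be mailed, followed up with a telephone call". The section does not say when the forms are sent out or when they are due back.
- **Randomisation and blinding.** In that follow-up call, "participants will be randomised by the researcher into intervention and control groups when they agree to be enrolled in the study". Concealment ends at the same moment: "group allocation will be concealed from the researcher until the participant has agreed to be in the study". Participants are not told their group and stay blinded. For the researcher the position is different: "Group allocation will not be concealed from the researcher when delivering the intervention or assessing outcomes".
- **Statistical analysis.** "The analyses of the trial will be based on (i) intention to treat and (ii) treatment received". Nothing is said about randomised people whose forms do not come back.
- **Sample size.** 178 per group, for a 1.3 kg difference in weight at 90% power and alpha 0.01, adjusted for clustering. The only attrition allowance stated is 20% loss to follow-up.

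**The concern.** Two stated rules do not fit together. One makes spoken agreement on the telephone the trigger for randomisation. The other makes an event that can only be established after a waiting period, the failure to return a form, a ground for exclusion. Followed literally, the plan lets someone agree, be allocated, and then be found ineligible.

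Two things are at stake. The first is the comparability of the groups. Whoever is responsible for the forms may already know the arm, and effort spent on reminders could differ between arms without anyone intending it. Selective loss after allocation cannot be reliably undone in the analysis. The second is precision: people removed for missing forms come off the 178 per group in addition to the loss to follow-up that was planned for.

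This is more than a detail that an article would leave to a fuller document. An analysis plan cannot change the order of the enrolment steps, and it may not be able to use data from someone who never signed consent.

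**Working it through.** **Order of steps, from the text**

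1. Information pack, then invitation letter, then telephone call (Participants).
2. Agreement in the call, then randomisation, and allocation becomes known to the researcher (Randomisation and blinding).
3. Signed consent and doctor's clearance returned: no place in the sequence is given. Non-return leads to exclusion (Participants).

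Step 2 depends on agreement and not on receipt of the forms. Step 3 can therefore fall after step 2.

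**The plan's own sample size**

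The 178 per group can be neither confirmed nor refuted, because the standard deviation (SD) and the clustering adjustment are not given. It can only be solved backwards:

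- Evaluable per group: 178 × (1 − 0.20) = 142.4.
- Two-sided alpha 0.01 (sidedness is not stated, so this is assumed) and 90% power: 2.576 + 1.282 ≈ 3.857.
- Implied SD of weight change with no design effect: 1.3 × √(142.4/2) / 3.857 = 2.84 kg. With a design effect of 2 it is 2.01 kg.

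**Effect on power**

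Let f be the fraction of randomised people excluded for missing forms, on top of the 20% loss. The document gives no value, so 5 to 20% is assumed. Starting from the stated 90%, power is Φ(3.857 × √(1 − f) − 2.576). The SD cancels out, and the design effect is taken as unchanged.

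| f | Evaluable per group, 142.4 × (1 − f) | Power | Randomised per group to keep 178, 178/(1 − f) |
|---|---|---|---|
| 0 | 142.4 | 90.0% | 178 |
| 5% | 135.3 | 88.2% | 188 |
| 10% | 128.2 | 86.1% | 198 |
| 15% | 121.0 | 83.7% | 210 |
| 20% | 113.9 | 80.9% | 223 |

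**Effect on the estimate**

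Let eA and eB be the excluded fractions in the two arms, and D the difference in mean outcome between people kept and people excluded, taken as equal in both arms. Removing the excluded shifts each arm's mean by e × D, so the between-arm difference shifts by (eA − eB) × D.

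- Equal exclusion of similar people (10% and 10%): shift 0. The cost is power only.
- 15% against 5%, D = 1 kg: 0.10 × 1 = 0.1 kg, and 0.1/1.3 = 8% of the target.
- 15% against 5%, D = 2 kg: 0.10 × 2 = 0.2 kg, and 0.2/1.3 = 15%.
- 15% against 5%, D = 3 kg: 0.10 × 3 = 0.3 kg, and 0.3/1.3 = 23%.

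The exclusion rates and D are all assumptions.

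**The case against.** The strongest reply is that the sequence is inferred. Forms could be enclosed with the invitation letter and come back before the call, at least for some people. Non-return sits among ordinary entry criteria, so a person without forms might be regarded as not yet enrolled. Figure 1, which outlines the design, is not available here and may show where the forms fall. This stands to the extent that exclusion after allocation is permitted by the text and not shown to be certain. It does not remove the conflict, because both randomisation and the end of concealment are tied in words to agreement in the call.

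A reader might also infer that the intention-to-treat comparison is broken or contradicted. The documents do not support that. The Statistical analysis section puts intention to treat first and nowhere says that randomised people with missing forms leave that analysis. Their handling is simply not stated.

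A reader might further infer that form return, reminders and medical clearance could all differ by arm. That too goes beyond the text. Participants are not told their group, nothing says that the doctor learns the arm, and nothing says that the clearance form differs between arms. The activity recommendations differ only for participants with BMI above 24.9 kg/m²; below that, the Intervention group and Control group sections give the same 30 minutes. What is left is the researcher, who knows the allocation and could follow up forms unequally.

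Finally, the figures are illustrations. A D of 2 to 3 kg is large beside a 1.3 kg target, power stays at about 81% or above over the assumed range, and the 20% loss to follow-up might already be meant to cover people who never start. All of this is fair and limits the size of the point, not its existence.

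**Conclusion.** The point holds as a conflict between the randomisation trigger and an exclusion criterion. As written, people can be excluded after the researcher knows their allocation. Bias follows only if exclusion differs by arm and those excluded differ in outcome, and the plausible route is unequal follow-up of forms by the unblinded researcher. Under the assumed values the shift is 0.1 to 0.3 kg against a 1.3 kg target. Loss of power is modest: from 90% to between 88% and 81% for 5 to 20% additional exclusion, assuming a two-sided test, an unchanged design effect, and a 20% loss allowance that does not already include these people. The documents do not show that such exclusions will occur, that they will be unequal, or that the intention-to-treat analysis will drop them. The case for acting is that the order of steps is cheap to settle before enrolment and hard to repair afterwards.

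**What to change.** Reconcile the Participants and Randomisation and blinding sections so that allocation follows the paperwork. Suggested wording: *The concealed allocation will be opened only once the signed consent form and the signed doctor's clearance form have both reached the study team.* Then state that:

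- from that point, form non-return is no longer a ground for exclusion;
- all randomised participants are analysed by intention to treat;
- any exclusion after randomisation that cannot be avoided, for example because there is no valid consent, is reported by arm with the reason.

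The re-ordering is the essential part. A rule to keep everyone randomised, without the re-ordering, would sit badly with people who never signed consent, whose data may not be usable.

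The cost is a few sentences of protocol text and a slightly later allocation contact. Some people who agree by telephone will drop out before randomisation, so a few more invitations may be needed to reach 178 per group.

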### Randomisation and blinding

During the follow up telephone call participants will be randomised by the researcher into intervention and control groups when they agree to be enrolled in the study. Participants will be block randomized within site. Microsoft Excel will be used to generate random numbers and the Statistical Analysis System (SAS) will be used to randomise these numbers into sets of two letters (A and B, representing the intervention and control groups respectively) by blocks of four to ensure a balanced sample size across both study groups [31]. The random numbers will be generated and packaged by a person external to the study so the group allocation will be concealed from the researcher until the participant has agreed to be in the study [32]. Participants will not be told whether they have been allocated to the intervention or control group and will remain blinded to group allocation. Group allocation will not be concealed from the researcher when delivering the intervention or assessing outcomes.

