### Sample size

To detect a reduction of 1.3 kg in weight and 0.5 kg/m^2 ^BMI between the intervention and control group (based on the COACH study effects on weight loss [24]) with a power of 90% (alpha 0.01), adjusting for clustering, and assuming a 20% loss to follow up, a sample size of 178 in each group is required.

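### Allocation is released on telephone agreement, but unreturned consent or clearance forms still exclude, so exclusions can follow randomisation

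*Protocol article*

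**What the plan says.** Recruitment, in the Participants section, runs from an information pack to a letter and then a call: "A personalised invitation letter will also be mailed, followed up with a telephone call". The last item in that section's list of exclusions is "non-return of a signed participant consent form and/or a signed doctor's clearance form".

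The Randomisation and blinding section fixes the moment of allocation: "During the follow up telephone call participants will be randomised by the researcher into intervention and control groups when they agree to be enrolled". It repeats the trigger when it describes concealment, where "group allocation will be concealed from the researcher until the participant has agreed to be in the study". From then on the researcher is open to the arm: "Group allocation will not be concealed from the researcher when delivering the intervention or assessing outcomes".

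The Statistical analysis section states that "The analyses of the trial will be based on (i) intention to treat and (ii) treatment received". It does not say how someone who was randomised but never returned a form is to be handled.

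**The concern.** The event that releases the allocation is agreement on the telephone. Eligibility also depends on two pieces of paper, and non-return can be established only after waiting for them. If the forms come back after the call, some people will have been allocated before their eligibility is known.

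Exclusions after allocation are not protected by randomisation. They do most harm when they can depend on the arm, and here the researcher knows the arm from the moment of agreement. Effort spent on obtaining forms, or a decision to stop waiting for them, could then differ between groups without anyone intending it. What is at stake is whether the set analysed as intention to treat is the set that was randomised.

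A related weakness has the same cause. Baseline weight is self-reported by telephone, and nothing places that report before allocation, so it may be taken by someone who knows the group.

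**Working it through.** **1. Order of events as written**

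| Step | Where stated | Tied to a point before allocation? |
|---|---|---|
| Information pack, letter, telephone call | Participants | Yes |
| Agreement on the call | Randomisation and blinding | Yes; it is the trigger |
| Allocation opened, arm known to researcher | Randomisation and blinding | – |
| Signed consent form received | Participants (exclusions) | No |
| Doctor's clearance form received | Participants (exclusions) | No |
| Baseline questionnaire | Data collection | No |

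**2. The conflict.** Take a person who agrees on the call, is allocated, and never returns a form. If that person is dropped, the first analysis is no longer by intention to treat. If the person is kept, the exclusion rule is not applied, and without signed consent the data may not be usable in any case. No analysis rule resolves this fully once the allocation has been opened. Only the order of steps does.

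**3. Bias.** Let p1 and p0 be the proportions excluded after allocation in the two arms, and d the difference in mean weight change between excluded and retained people, taken as equal in both arms. Each arm's retained mean is shifted by −p × d, so the bias in the group difference is −(p1 − p0) × d. The documents give none of p1, p0 or d. Purely to show how much the answer depends on them:

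- gap of 10 points, d = 2 kg: 0.10 × 2 = 0.20 kg, which is 0.20 / 1.3 = 15% of the target difference;
- gap of 5 points, d = 1 kg: 0.05 × 1 = 0.05 kg, about 4% of it;
- no gap: zero.

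Equal rates do not guarantee zero bias if different kinds of people are lost in the two arms.

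**4. Precision.** The Sample size section gives 178 per group for 1.3 kg, "with a power of 90% (alpha 0.01), adjusting for clustering" and allowing 20% loss to follow-up. It gives neither the standard deviation nor the design effect, so 178 cannot be reproduced. It can be worked backwards, taking alpha as two-sided and the design effect as 1 (both assumptions):

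- evaluable per group: 178 × 0.8 = 142.4
- implied SD = 1.3 × √(142.4 / 2) / (2.576 + 1.282) = 2.84 kg

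A design effect of 1.25, 1.5 or 2 would imply 2.54, 2.32 or 2.01 kg. At 2.84 kg, with a further proportion x excluded after randomisation in both arms, evaluable per group is 178 × (1 − x) × 0.8, and the number needed to keep 90% power is 142.4 / (0.8 × (1 − x)):

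| x (assumed) | Removed per group | Evaluable per group | Power | Needed per group |
|---|---|---|---|---|
| 0 | 0 | 142.4 | 90% | 178 |
| 5% | 9 | 135.3 | 88% | 188 |
| 10% | 18 | 128.2 | 86% | 198 |
| 20% | 36 | 113.9 | 81% | 223 |

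The 20% allowance is labelled loss to follow-up. The article states no separate allowance for exclusions of this kind.

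**The case against.** The article never says when the forms are sent, due or checked. Non-return sits in a list with diagnoses that would naturally be screened before enrolment. Figure 1, which outlines the design, is not available here and may show the order, and a condensed article commonly leaves the mechanics of form return to the full protocol. Forms may therefore be collected before the call in practice. This limits the point to what the text permits. It does not remove it, because the article goes beyond silence: it names agreement as the trigger twice, and once places it during the call.

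Four stronger readings are tempting, and the documents do not support them.

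- *Everyone who fails to return a form will be randomised and then excluded.* The text allows this; it does not establish it.
- *Doctors would refuse clearance more often in the intervention arm, because of the 60–90 minutes of activity.* Nothing says that the clearance form depends on the arm or states an activity volume. Participants are not told their group, which fits poorly with an arm-specific form. The longer duration also applies only above a BMI of 24.9 kg/m²; intervention participants in the healthy range are recommended 30 minutes, as in the control arm.
- *The bias is about 0.2 kg.* The inputs to that figure have no source, and a 2 kg difference between excluded and retained people is larger than the effect the trial is designed to detect.
- *The excluded come out of the 178.* The Sample size section does not say whether 178 counts telephone agreements or people with complete paperwork. The Outcome measures section equates 25% of the intervention group with 45 people, so about 45 / 0.25 = 180 in the group, with baseline measurements taken among them. That is compatible with 178 counting enrolled people, in which case the power losses shown would not arise.

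**Conclusion.** The point stands as a conflict between the stated trigger for allocation, the form-based exclusion and the intention-to-treat analysis. Following the article as written, people can be excluded after allocation by a process open to influence from a researcher who knows the arm.

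The direction and size of any bias cannot be estimated from the documents. The loss of power is an illustration that rests on assumed exclusion rates, a back-solved standard deviation, no clustering, a two-sided alpha, and 178 being the number randomised on the call. The conclusion depends on none of these figures, only on the order of steps. It should be corrected, because the remedy is specific and cheap, and an analysis plan written later cannot undo an allocation already revealed.

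**What to change.** In the Randomisation and blinding section, state that the next allocation is opened only after (a) both signed forms have been received and (b) the main baseline telephone questionnaire, including self-reported weight and height, has been taken. Non-return is then recorded as a screen failure before randomisation, and everyone allocated stays in the intention-to-treat set. If forms are already collected before the call, one sentence saying so settles that part.

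One exception is needed. The validation sub-group is drawn from the intervention group only, so its members cannot be identified until the arm is known. Its measured height, weight and waist, food diary, accelerometer week and the self-reports completed at the end of that week should stay after allocation and be used for validation only. The baseline values for the trial comparison come from the questionnaire taken before allocation.

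The cost is a short delay between agreement and allocation and possibly one extra call per participant. About 45 sub-group members may also have to answer the activity, sedentary and nutrition items twice at baseline. No new instruments are needed.

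### A single fixed block size of four within site, with a recruiter who also allocates and is unblinded afterwards, weakens concealment: up to one third of assignments could be known in advance

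*Protocol article*

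**What the plan says.** All the relevant rules stand in the Protocol article, section Randomisation and blinding, unless noted.

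- **Strata:** "Participants will be block randomized within site". There are four sites, two urban and two rural (section Participants).
- **Blocks:** two arms, A and B, are arranged "by blocks of four to ensure a balanced sample size across both study groups". No other block size is mentioned.
- **Who allocates, and when:** on the recruitment call, "participants will be randomised by the researcher into intervention and control groups when they agree to be enrolled in the study".
- **Safeguard:** "The random numbers will be generated and packaged by a person external to the study". The article gives the purpose as "so the group allocation will be concealed from the researcher until the participant has agreed to be in the study".
- **Blinding afterwards:** "Group allocation will not be concealed from the researcher when delivering the intervention or assessing outcomes".

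**The concern.** Packaging by an outside person hides the list. It does not hide what can be worked out from assignments already made. With 1:1 blocks of four, a person who knows the block size and has followed a site's allocations always knows the fourth assignment. That person also knows the third whenever the first two were the same. The article puts enrolment, allocation and later unblinded contact with the researcher, so the person best placed to make this inference is also the one seeking agreement.

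Agreement is sought by telephone. A recruiter who knows or suspects the next arm could, without intending to, place a call earlier or later, or press harder with someone who sounds keen. More motivated participants could then collect in one arm. The primary outcome is self-reported weight and BMI (section Outcome measures), and the target difference is 1.3 kg (section Sample size). The planned adjustment is for residence, age and sex (section Statistical analysis), which would not remove a difference in motivation.

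**Working it through.** **Inputs.** Block size 4, two A and two B per block, four sites, researcher unblinded after allocation (sections Randomisation and blinding, and Participants). Total planned: 2 x 178 = 356 (section Sample size), used only to turn shares into counts. The article states no predictability figure, so there is none to reproduce.

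**Certain assignments, one fully informed recruiter per site.** A block has 6 equally likely orders.

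- AABB and BBAA each fix positions 3 and 4: 2 certain assignments.
- The other four orders fix position 4 only: 1 certain assignment.
- Expected number per block: (2 x 2 + 4 x 1)/6 = 4/3.
- Share: (4/3)/4 = 1/3 = 33.3%. By position it is 0, 0, 1/3 and 1.
- Count: 356/4 = 89 complete blocks; 89 x 4/3 = 118.7, about 119. Incomplete final blocks lower this slightly: a simulation with 90 participants per site gave 32.6%.

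**Best guess.** Guess the arm with more places left, and toss a coin when tied.

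- Position 1: 1/2. Position 2: 2/3. Position 4: 1.
- Position 3: 1/3 x 1 + 2/3 x 1/2 = 2/3.
- Average: (0.500 + 0.667 + 0.667 + 1)/4 = 70.8%, against 50% with no information.

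**Recruitment at a site shared equally and at random by k researchers who do not exchange allocations but know where blocks begin.** An assignment is certain only if the researcher making it also made both earlier assignments to the arm that is already full, which has probability 1/k². The share becomes (1/3)/k².

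- k = 1: 33.3%
- k = 2: 1/12 = 8.3% (356/12, about 30 participants)
- k = 3: 1/27 = 3.7%

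**Other block schemes, one fully informed recruiter.** For a fixed block of 2m the certain share is 1/(m + 1). For mixed sizes the figures come from a simulation of 200,000 assignments, 90 per site, in which the recruiter knows which sizes are in use but not their order.

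| Scheme | Certain in advance | Best guess correct |
|---|---|---|
| Fixed 4 (the plan) | 33.3% | 70.8% |
| Fixed 6 | 25.0% | 68.3% |
| Fixed 8 | 20.0% | 66.6% |
| Random order of 4 and 6 | about 5.5% | about 69% |
| Random order of 4, 6 and 8 | about 2.3% | about 68% |

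**What it could do to the estimate (assumption, not from the article).** By symmetry, the known assignments make up the same share of each arm. Suppose participants enrolled under a known A and a known B differ by d kg in expected weight change, and nobody else is selected. The bias is then the certain share times d.

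- d = 0.5 kg: 0.17 kg at a share of 1/3, 0.04 kg at 1/12.
- d = 1 kg: 0.33 kg at a share of 1/3, 0.08 kg at 1/12.

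The largest of these is 0.33/1.3, about a quarter of the target difference. The article gives no basis for any particular d.

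**The case against.** Several points on the other side stand and limit the finding.

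- **Concealment is not abolished.** The researcher holds no list, the first assignment in each block stays unpredictable, and at least two thirds of assignments are never certain. A reader might infer that concealment is defeated, but the text supports only that it is weakened.
- **One third is a maximum.** The article says the researcher is unblinded when delivering the intervention and assessing outcomes. It does not say that one person sees every earlier allocation at a site. Randomisation and blinding speaks of the researcher in the singular, but Data collection has several researchers administering questionnaires, so recruitment may be shared.
- **Steering by weight is not shown.** A reader might infer that heavier people would be steered to one arm. There is no weight or BMI entry criterion, weight is collected in the baseline questionnaire, and nothing indicates that the recruiter knows it before randomising.
- **Discretion and incentive are limited.** Everyone referred is invited, within a set window, by letter before the call. Both arms receive active coaching, a pedometer and booster calls. This reduces the scope for selection, but call order and persuasion remain open.
- **A condensed article may omit safeguards.** Whether the block size was withheld from recruiters could well be in the full protocol, and that silence is not held against the plan. The single block size, however, is a rule the article states, not a detail left out.

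**Conclusion.** The point holds as a weakness of moderate weight. One fixed block size of four within site, combined with a recruiter who allocates and is then unblinded, means that external packaging alone cannot guarantee the concealment the article claims.

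The share of assignments certain in advance is at most one third (about 119 of 356), with best guesses right 70.8% of the time. These figures assume one recruiter per site who knows the block size, follows block boundaries and sees all earlier allocations there. The certain share drops to about 8% if two recruiters split a site equally and do not share allocations.

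The arithmetic is exact under those conditions; whether they apply is uncertain. The plausible route to bias is call timing or persuasion of more motivated participants. A reader might go further and infer that selection takes place, but the article shows only the opportunity. The sample size calculation is unaffected.

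**What to change.** Have the external person generate each site's list with block sizes in random order, such as 4, 6 and 8, and withhold the sizes from the recruiting researcher. If recruitment has begun, apply this to the unused remainder of the list.

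This cuts certain assignments from 33% to about 2%. It should not be presented as restoring unpredictability: best-guess accuracy falls only from 70.8% to about 68%, because any balanced block favours the under-filled arm. If the team wants to address that remainder, recruitment could be done by someone who does not see earlier allocations at the site.

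The cost is small. An external person already prepares the list, and the sample size does not change. When recruitment ends partway through a block, the arms at a site can differ by at most half the block size: up to 4 participants with a block of 8, against 2 with a block of 4.
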